#### Testing the effect of CCT on self-efficacy

Among participants receiving CCT, a linear model including fixed effects for site, time and baseline self-efficacy will assess changes on the New General Self-Efficacy Scale and the Cough Self-Efficacy Scale.

### Main analyses for observational extension phase

#### Descriptive analyses at 6 and 12 months

We will report the frequency and proportion of patients who continue on their assigned treatment, switch to an alternative treatment, discontinue all treatment (ie, are on no treatment), enrol in another clinical trial and continue to use techniques learnt during the CCT programme. Among those who switch, we will describe the treatments they switch to (eg, morphine, pregabalin, gabapentin, amitriptyline, codeine). For those who switch treatments, discontinue all treatment or enrol in another clinical trial, we will descriptively summarise the reasons (eg, adverse effects, lack of benefit) by initial randomised group and by treatment exposure at the time of the switch or discontinuation. For CCT participants, reasons for not continuing techniques will be documented.

#### Analysis of patient-reported outcomes at 6 and 12 months

Linear mixed-effects models will estimate changes from week 6 (baseline for the extension phase) to 6 and 12 months for the MCSQ, CS-VAS and LCQ. Models will include time, treatment group (time-varying), site and baseline score as fixed effects and participant-level random intercepts.

Treatment group will be defined as a time-varying categorical fixed effect based on the patient’s self-reported treatment at each follow-up visit. The categories will be: (1) on morphine, (2) on pregabalin, (3) on another antitussive, (4) in a clinical trial or (5) not on any treatment.

The primary analysis will be conducted under a missing-at-random assumption using maximum likelihood estimation. If missing outcome data is ≥15%, an MNAR sensitivity analysis will be performed. Marginal means (95% CI) at each timepoint will be estimated. Between-group differences in mean changes from baseline at 6 and 12 months (95% CI) will be calculated using post hoc contrasts. P values for the treatment effect at months 6 and 12 will be reported at the conventional two-sided 0.05 level without adjustment for multiple comparisons. These p values will be interpreted cautiously given the observational and exploratory nature of these analyses.

### Analysis of safety outcomes

We will report all safety outcomes descriptively according to the as-treated population. The as-treated population will include analysing those based on the treatment received, regardless of their initial randomisation. During the randomised phase, AE categories—including participants with any AE, treatment-related AEs, SAEs and discontinuation due to AEs—will be reported descriptively at 6 weeks. AEs occurring in ≥10% of participants in a single group at 6 weeks will be highlighted. In addition, we will specifically monitor and report the incidence of the most common side effects of each study drug. For morphine, this includes constipation and drowsiness/sedation. For pregabalin, this includes dizziness, somnolence and peripheral oedema. Safety outcomes during the observational extension will be similarly reported based on participants’ treatment exposure at 6 and 12 months.

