### Gaps in the literature

Although current evidence supports the individual efficacy of low-dose morphine^11
13^ and pregabalin,^8^ no head-to-head trials have compared these treatments. The routine use of these agents highlights the need for a large randomised trial directly comparing their benefits and harms.

Furthermore, while guidelines recommend non-pharmacological interventions, randomised trial evidence remains limited to two small studies, with uncertainty regarding durability beyond 3 months,^10^ the specific intervention components that drive benefit, and the factors influencing scalability and broader implementation. This highlights the need for a rigorous evaluation of the effectiveness of a scalable virtual intervention, as well as its fidelity and implementation considerations.

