## Discussion

Despite guidelines recommending neuromodulators for the treatment of RCC/UCC and their frequent prescription among clinicians, there remains no head-to-head evidence on the comparative benefits and potential long-term harms of these treatments. FORTITUDE will provide important evidence to guide clinicians on which neuromodulator to prescribe for their patients.

FORTITUDE will also represent the largest trial to evaluate the effectiveness of a virtual CCT programme. Data from utility scores, diaries, attendance, checklists and interviews capturing intervention intensity and patient experience will support cost-effectiveness and acceptability analyses.

A 2×2 factorial design allows simultaneous evaluation of two interventions. Since our objective is to compare low-dose morphine versus pregabalin and virtual CCT versus no CCT, this design provides efficient estimation of main effects with fewer participants than two separate trials. In addition, the trial will study these interventions in combination. While one trial has evaluated pregabalin in combination with speech therapy,^8^ no trials have evaluated non-pharmacological interventions with low-dose morphine.

Although we propose a 2×2 factorial trial with combined interventions, our primary analysis assumes no interaction between neuromodulators and CCT. For separate estimation of main effects, we will assume no interaction between neuromodulators and CCT. As neuromodulators and CCT act through distinct mechanisms—neurobiological versus behavioural modulation of the cough reflex—we believe this assumption may be biologically plausible. The main analysis will independently estimate the effects of neuromodulator treatment (morphine vs pregabalin) and CCT (virtual CCT vs no CCT), with the trial powered accordingly. While we considered a 3×2 factorial design including a placebo group, we opted against this design to keep the study pragmatic and to not withhold active treatment. The primary objective of this trial is to assess the comparative effectiveness of commonly used treatment strategies rather than to estimate efficacy relative to placebo. Because participants will be randomised, any placebo effects are expected to be distributed equally across the active treatment arms and therefore should not bias comparisons between interventions.

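### Harms in the randomised 6-week phase get no between-arm estimate or interval, although the trial is justified by a direct comparison of harms and binary efficacy outcomes do get one

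*Protocol article*

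**What the plan says.** All points are in the protocol article.

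- **Method and population (Analysis of safety outcomes).** "We will report all safety outcomes descriptively according to the as-treated population". The population is then defined: "The as-treated population will include analysing those based on the treatment received, regardless of their initial randomisation".
- **Highlighting (same section).** "AEs occurring in ≥10% of participants in a single group at 6 weeks will be highlighted". The section does not say whether a group is a drug arm, a CCT arm or one of the four factorial cells.
- **Named side effects (same section).** "we will specifically monitor and report the incidence of the most common side effects of each study drug". These are listed drug by drug: constipation and drowsiness/sedation for morphine; dizziness, somnolence and peripheral oedema for pregabalin.
- **Safety outcomes.** Four are defined (any AE, treatment-related AEs, serious AEs, and AEs leading to discontinuation), each as a proportion for each intervention and not as a difference.
- **Rationale (Gaps in the literature).** "The routine use of these agents highlights the need for a large randomised trial directly comparing their benefits and harms". The Discussion adds that "there remains no head-to-head evidence on the comparative benefits and potential long-term harms of these treatments".
- **Rank (Objectives).** Effectiveness is co-primary; safety and tolerability are secondary or exploratory.
- **Contrast (Secondary responder analyses at 6 weeks).** Binary responder outcomes get absolute risk differences with 95% CIs from an identity-link model adjusted for site.

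**The concern.** The protocol states a comparative purpose for harms but fixes a reporting method with no comparison in it. The gap is in stated text, since the safety section names both the method and the population. It is also out of step with the rest of the plan. Responder proportions get a risk difference and an interval, and the extension-phase patient-reported outcomes, which compare non-randomised groups, get between-group differences, intervals and p values. The randomised 6-week harms data, where a comparison is cleanest, get none.

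If the two drugs turn out similar on cough frequency, tolerability will weigh heavily in the choice between them. Two percentages without an interval do not tell a reader how large a difference the data allow. The 10% rule does not fill that gap, because it looks at each group alone.

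**Working it through.** **1. Arm size.** The Sample size section gives 62 per drug arm and four cells of 31. The 62 reproduces: standardised effect 0.357/0.6 = 0.595; a two-sample t test at two-sided alpha 0.025 and 80% power needs 54.97, so 55 per arm; 55/0.9 = 61.1, so 62 per arm and 124 in total.

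**2. What the 10% rule needs.** 0.10 × 62 = 6.2, so an AE is highlighted in a drug arm at 7 or more events.

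**3. Chance that exactly one drug arm reaches the rule when the true rates are equal.** Let q = P(X ≥ 7) with X ~ Binomial(62, p). The chance that exactly one of two independent arms reaches the rule is 2q(1−q). The document gives no AE rates for the trial arms, so p is an assumption, shown over a range:

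| Assumed true rate in both arms | q | 2q(1−q) |
|---|---|---|
| 5% | 0.035 | 0.07 |
| 8% | 0.225 | 0.35 |
| 10% | 0.427 | 0.49 |
| 11% | 0.530 | 0.50 |
| 12% | 0.626 | 0.47 |
| 15% | 0.841 | 0.27 |
| 20% | 0.976 | 0.05 |
| 25% | 0.998 | 0.004 |

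The expression cannot exceed 0.50, which it reaches when q = 0.5. It is 0.45 or more only for true rates of about 9.2% to 12.3%.

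**4. Sensitivity to the definition of group.** With 56 per drug arm after 10% dropout (rule met at 6 events), the figure is 0.11 at 5%, 0.50 at 10% and 0.04 at 20%. If a group is a cell of 31 (rule met at 4 events, q = 0.376 at a 10% rate), the chance that some but not all four cells reach the rule is 1 − q⁴ − (1−q)⁴ = 0.83.

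**5. What a between-arm estimate would show.** The counts are illustrative, 62 per arm, with Newcombe 95% intervals:

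- 7/62 v 6/62: only the first arm is at 10% or more (11.3% v 9.7%); difference 1.6 points (−9.8 to 13.1).
- 3/62 v 9/62 discontinuations: difference 9.7 points (−1.1 to 21.0).
- 12/62 v 22/62: difference 16.1 points (0.4 to 30.9).

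**6. Precision to expect.** The Wald half-width is 1.96 × √(2p(1−p)/62): 10.6 points at p = 10%, 14.1 at 20% and 16.1 at 30%.

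**The case against.** The case on the other side has weight, and several parts of it stand.

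- **Descriptive safety reporting is common, and safety is not a co-primary objective.** True. The rationale in Gaps in the literature is a statement of need, and the sentence on harms in the Discussion concerns long-term harms, so it bears less on week 6. This lowers the priority. It does not explain why responder proportions get an interval and AE proportions do not.
- **The 10% rule is a display rule.** It is not called a comparison or a signal test, and it may mean that an AE reaching 10% in any group is shown for all groups. A reader might infer that the plan will single out one drug by chance about half the time. The text does not support that: half is the ceiling, it needs a true rate near 10% in both arms, and the document gives no AE rates for those arms.
- **Differences under the threshold are not lost.** A reader might infer that a real difference of less than 10 points can never be highlighted. That is wrong: at true rates of 3% and 12%, the second arm reaches the rule with probability 0.63. The four safety outcomes and the named side effects are reported whatever their frequency.
- **As-treated grouping should matter little for the drugs at 6 weeks.** Concomitant therapy bars switching to the other neuromodulator in this period, so received and randomised drug should nearly coincide. A reader might also infer that patients assigned to CCT who attend nothing are counted as no CCT. The section does not say how they are classed, so that is one possible reading only.
- **The statistical analysis plan may add intervals, and readers can derive crude differences from published counts.** The plan is a supplement that is not shown, and descriptive reporting does not strictly exclude an interval. But the article states method and population without one, and a difference derived by a reader would be unplanned and based on treatment received.

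**Conclusion.** The point holds in a limited form. For the randomised 6-week phase the protocol article fixes safety reporting as descriptive and as-treated, with no between-arm estimate or interval. This sits badly with its stated need to compare harms directly and with its own handling of binary efficacy outcomes.

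The 10% rule cannot stand in for a comparison. For an AE with a true rate near 10% in both arms, it would be met in exactly one drug arm up to about half the time, but in only about 7% of cases at a 5% rate and 5% at a 20% rate. These figures assume that a group is a drug arm of 62, that the true rates are equal and that the arms are independent.

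The document does not support a claim that the safety results will mislead or that as-treated grouping will distort the 6-week drug comparison. This is a cheap improvement of low to moderate priority. No primary conclusion depends on it.

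**What to change.** - For the 6-week phase, report the four listed safety outcomes and the named side effects by randomised arm. Give risk differences and 95% CIs for morphine versus pregabalin and for CCT versus no CCT, and no p values. The responder section already sets out a usable method; where events are sparse, a Newcombe interval will serve.
- Report each named side effect for both drugs, not only for the drug under which it is listed.
- Say what a group is in the 10% rule. For any AE highlighted under it, show both arms and the difference with its interval.
- Keep the as-treated tables as supportive at 6 weeks and for the extension, and state how CCT receipt is classed.

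The cost is a few sentences in the analysis plan and one more column in tables already planned. It needs no extra patients or data. The downside is that the intervals will be wide (about ±11 to ±16 points for rates of 10% to 30%) and must be labelled as not adjusted for multiplicity.

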### Concomitant therapy

Sites will follow the 2020 European Respiratory Society guidelines for the treatment of chronic cough.^6^ During the 6-week randomised phase, use of morphine, pregabalin and non-pharmacological cough interventions outside of the allocated treatment will generally not be permitted to avoid confounding. During this phase, patients will also not be allowed to co-enrol in other clinical trials involving investigational medicinal products for the treatment of RCC/UCC.

Patients who do not respond to their allocated treatment (morphine or pregabalin) will not be permitted to switch to the other neuromodulator or alternative antitussives (eg, gabapentin, amitriptyline, codeine, dextromethorphan) during the 6-week randomisation period. This is to preserve the integrity of treatment allocation and minimise treatment contamination.

Once patients complete the 6-week randomised phase and enter the observational extension, patients can take any concomitant treatments, including switching neuromodulators, engaging in adjunctive therapies or enrolling in other clinical trials of RCC/UCC. We will closely monitor and document therapies taken during the observational extension for up to 1 year.

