#### Safety outcomes

The proportion of patients with any adverse event (AE) for each intervention at 6 weeks, 6 months and 12 months.The proportion of patients with treatment-related AEs for each intervention at 6 weeks, 6 months and 12 months.The proportion of patients with serious adverse events (SAEs) for each intervention at 6 weeks, 6 months and 12 months.The proportion of patients with AEs leading to treatment discontinuation for each intervention at 6 weeks, 6 months and 12 months.

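### Extension adverse events are grouped by treatment status at the 6- and 12-month visits, which can move an event that caused stopping or switching away from the drug taken when it occurred

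*Protocol article*

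**What the plan says.** All of the following is in the Protocol article.

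- **Analysis of safety outcomes, general rule.** Safety is described in the as-treated population: "The as-treated population will include analysing those based on the treatment received, regardless of their initial randomisation".
- **Analysis of safety outcomes, extension.** Safety is reported in a similar way, based on "treatment exposure at 6 and 12 months".
- **Safety outcomes.** One listed outcome is "The proportion of patients with AEs leading to treatment discontinuation for each intervention at 6 weeks, 6 months and 12 months". Any AE, treatment-related AEs and serious AEs are listed for the same three times.
- **Analysis of patient-reported outcomes at 6 and 12 months.** This is the only place that defines treatment groups in the extension. It uses the participant's "self-reported treatment at each follow-up visit", and one category is being on no treatment.
- **Descriptive analyses at 6 and 12 months.** Reasons for switching or stopping are summarised "by initial randomised group and by treatment exposure at the time of the switch or discontinuation".
- **Concomitant therapy.** After week 6, "patients can take any concomitant treatments, including switching neuromodulators, engaging in adjunctive therapies or enrolling in other clinical trials of RCC/UCC". Therapies taken in the extension are to be documented.

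**The concern.** Treatment status at a follow-up visit comes after the AEs of the preceding interval and partly results from them. With assessments at 6 and 12 months after randomisation, the intervals last roughly four and a half and six months, and participants may change treatment at any point. Someone who stops morphine in month 3 because of an AE is off it, or on something else, by month 6. Grouping by status at the visit takes that event out of the morphine row and puts it where it does not belong.

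At stake is the extension's long-term safety description. The abstract gives long-term safety as one purpose of the extension, and the Discussion motivates the trial partly by the lack of comparative evidence on long-term harms. A descriptive table that lists events under the wrong drug still misleads its reader.

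**Working it through.** The plan gives no figure on this point to reproduce. The check sets the rules side by side and then illustrates direction and range on assumed rates.

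**1. Which exposure does each rule use?**

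| Section | Exposure used |
|---|---|
| Analysis of safety outcomes, general rule | Treatment received |
| Analysis of safety outcomes, extension | Exposure at 6 and 12 months |
| Patient-reported outcomes at 6 and 12 months | Self-report at each visit |
| Descriptive analyses, reasons for change | Exposure when the participant switched or stopped |
| Safety outcomes, AEs leading to discontinuation | Must be the drug that was discontinued |

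The second row, read with the third, cannot deliver the fifth. Among participants on a drug at the visit, the only ones who can have discontinued that drug because of an AE in the interval are those who have since restarted it. The fourth row shows that the plan already uses a suitable rule, but only for reasons.

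**2. Direction.** Take participants on one drug at the start of an interval. Let p be the true AE risk on that drug, s the probability of being off it by the visit after an AE, and s0 the same probability without an AE.

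- Risk shown in the drug's row: p(1 − s) / [p(1 − s) + (1 − p)(1 − s0)]
- Risk shown among those now off the drug: ps / [ps + (1 − p)s0]

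The first expression equals p when s = s0 and falls below p whenever s > s0. The row therefore understates the risk whenever AEs make stopping more likely.

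**3. Range.** The documents give none of p, s or s0. Assumed values: p = 20%, 30% or 40%; s = 25% to 75%; s0 = 10% or 20%.

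Worked case with p = 0.30, s = 0.50, s0 = 0.10:

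- Drug's row: 0.30 × 0.50 = 0.15 with an AE and 0.70 × 0.90 = 0.63 without. 0.15 / 0.78 = 19.2%.
- Off-drug row: 0.30 × 0.50 = 0.15 with an AE and 0.70 × 0.10 = 0.07 without. 0.15 / 0.22 = 68.2%.

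| True risk | Shown in the drug's row | Shown among those off the drug |
|---|---|---|
| 20% | 6.5% to 19.0% | 23.8% to 65.2% |
| 30% | 10.6% to 28.7% | 34.9% to 76.3% |
| 40% | 15.6% to 38.5% | 45.5% to 83.3% |

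Attribution at onset, with all who were exposed as denominator, returns p. The illustration follows starters of one drug only. Participants who switch into a drug after an AE on another one would carry that event into the new drug's row, so a published row could also gain events that are not its own.

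**The case against.** The strongest reply concerns wording. The extension sentence says safety will be similarly reported, which points back to the treatment-received rule. The mention of 6 and 12 months may give only the reporting times, parallel to the 6-week report in the same section. Since the visit-status reading nearly empties a listed outcome, the authors may not have meant it. The section that defines treatment by visit concerns patient-reported outcomes and does not govern safety. This reading is possible, so misattribution is a likely consequence of the wording and not a certainty. But treatment received does not settle the matter once a participant has received two treatments, and the only extension definition on the page is by visit.

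Second, the plan partly covers the problem. Reasons for stopping, including adverse effects, are summarised "by treatment exposure at the time of the switch or discontinuation", extension therapies are documented, and investigators assess causality. This stands for reasons for stopping. It does not fix where events are counted for any AE, treatment-related AEs or serious AEs.

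Third, safety is a secondary or exploratory objective, extension safety is descriptive, and the article acknowledges confounding and selection in the extension. That limits the weight of the point. It does not excuse a grouping rule that can list an event under the wrong treatment. Windows and data fields may properly sit in the analysis plan, but here the article states a rule.

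Two stronger readings are tempting and are not supported:

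- **Uneven ascertainment.** The section names side effects by drug: "For morphine, this includes constipation and drowsiness/sedation. For pregabalin, this includes dizziness, somnolence and peripheral oedema". A reader might infer that each symptom is asked about only in its own arm, which would bias an open-label comparison. Nothing says so. The section on AEs and SAEs requires any adverse health change to be documented, without distinction by arm.
- **A count of lost discontinuations.** A reader might apply the 5% discontinuation rate from the pregabalin trial cited in the Introduction to the 62 participants per drug. That rate does not carry over to morphine, and anyone who stops in the first six weeks belongs to the 6-week table.

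**Conclusion.** The concern holds for the extension safety tables. On the plain reading, AEs after week 6 are grouped by a status that follows the event and can be caused by it. This understates harms of the drug that was stopped and conflicts with three other statements in the article. The size is unknown because the documents give no extension AE, stopping or switching rates. The ranges above are illustrations and show direction only as far as AEs make stopping more likely (s > s0). The 6-week safety table is not affected, and neither are the sample size and the efficacy analyses. The reasons-for-stopping summary is a partial safeguard. The point merits a correction before the extension data are tabulated, and preferably before recruitment, which is planned from September 2026, because the dates it needs are best collected prospectively.

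**What to change.** Amend the extension sentence in Analysis of safety outcomes so that:

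1. each extension AE is attributed to the treatment being taken at onset, or to one recently stopped within a prespecified window;
2. the denominator for each treatment is everyone exposed to it during the interval, not only those on it at the visit;
3. AEs leading to discontinuation are counted against the treatment that was discontinued;
4. a parallel table gives the same outcomes by randomised group.

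The cost is a short change of wording, AE onset dates and treatment start and stop dates in the case report form (the plan already commits to documenting extension therapies), and slightly more tabulation. A participant can appear in more than one treatment's denominator, which the table should state.
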